### Study population

The participants included in the ROAD study will be patients with renal anemia in the context of end-stage kidney disease on dialysis (both hemodialysis and peritoneal dialysis), and on Roxadustat treatment who consent to the study. The de-identified data from the provincial dialysis registry of dialysis patients with renal anemia will be serves as a control group. The study was approved by the Institutional Review Board at Sichuan Provincial People’s Hospital (2019 − 196). The informed consent obtained from study participants will be written.

Inclusion criteria include:①Age 18–90 years; ②End-stage kidney disease patients who are receiving maintenance hemodialysis or peritoneal dialysis;③Dry weight 45–160 kg; ④Renal anemia, defined as HGB < 130 g/(male), HGB < 120 g/L(female) or HGB is maintained normal by ESA; ⑤willing to participate in the study with informed consent. Exclusion criteria includes:①patients with pre-existing malignancy; ②Known history of hematological disorders including myelodysplastic syndrome, multiple myeloma, hereditary hematologic disease such as thalassemia, sickle cell anemia, pure red cell aplasia, or other known causes for anemia other than CKD or dialysis. ③Patients who cannot complete the follow-up study.

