### Data collection

The de-identified data were collected in REACH via Research electronic data capture (REDCap [14, 15], hosted at Sichuan Provincial People’s Hospital) pre-designed forms from baseline to week 108/2 years. The table with an identification code will be kept within the study site in a secure way. The provision of de-identified medical records will be required for judication for the MACE outcome. Participants will be followed up to 2 years except that they withdraw from the study, have their dialysis type changed, receive kidney transplantation or have lost follow up.

Dialysis data from each study site in the provincial dialysis registry will be collected via a dialysis software provided by the Sichuan Quality Control Center of Renal Disease at the end of the first and second study year.

A questionnaire focusing on medical expense for the participants will be collected at the end of the first and second year of the study.

The target sample size of the ROAD participant is greater than 250 basing on the MACE incidence of at least 20% [16, 17] within 2 years among ROAD and dialysis registry cohort, basing on noninferiority assumption with a marginal difference of 0.02 (10% of MACE incidence), actual difference of -0.08 (40% of MACE incidence),α = 0.05 and 1-β = 0.8, allowing a drop rate of 15%, using ‘Non-Inferiority Tests for the Difference Between Two Proportions’ of PASS software 15.0.5.

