### Quality control

The investigators will be trained before initiation of the study. A multi-disciplinary team will provide consultation on adjustment of Roxadustat dosage based on HGB level if needed during the study. An online video and handbook will be provided to guide the data entry. The online forms will be provided for data validation to minimized errors with data entry. Data monitoring will be carried out to make sure the accuracy of the data entry. The main outcome of MACE will be judicated independently by two trained doctors using de-identified medical records. A third doctor will be consulted if there are any disagreements. The questionnaire on economic costs will be randomly selected and double-checked with medical insurance department to ensure the authenticity. The data will be locked once the data cleaning completes, and the analysis plan will be prepared and run independently by two statisticians.

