### Data analysis

The comparison in primary outcomes between the ROAD cohort and the registry data will be performed using Multiple Cox regression of risk factors and propensity score method will also be applied as a sensitivity analysis. The medical economic costs will be compared between ROAD cohort and registry control group using the whole population as well as populations stratified by hospital levels, regions, comorbidities.

The efficacy on HGB of Roxadustat in the treatment of anemia of the whole cohort as well as the pre-defined subgroups (including patients with evidence of erythropoietin resistance, patients with chronic inflammation, patients with impaired iron metabolism, and patients on hemodialysis or peritoneal dialysis) will be analyzed in intention-to-treat and per-protocol ROAD population. Treatment heterogeneity will be tested by adding an interaction term to the statistical models.

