## Discussion

Anemia is a common complication in patients with chronic kidney disease, especially in those on dialysis. Treatment of renal anemia is associated with improvement in cardiovascular function, and health related quality of life, reducing requirements for blood transfusion and hospitalization [18–20]. Erythropoiesis-stimulating agents are one of main treatments for anemia in dialysis [21]. Higher dosage of erythropoiesis-stimulating agents, however, is associated with risk of stroke [22–24], however, potential risks may occur according [25–28]. In addition, more than 10% patients were hyporesponsive to ESA [29, 30].

Roxadustat, a potent, reversible, HIF-PHI that mimics the natural response to hypoxia results in target genes involved in erythropoiesis [31–33]. The meta-analysis of randomized controlled trials showed that Roxadustat can improve hemoglobin levels and iron metabolism in both dialysis-dependent and non-dialysis-dependent chronic kidney disease [34, 35]. However, its long term efficacy and safety needs to be investigated.

This study is designed to systemically assess the impact of Roxadustat on dialysis patients in the real-world practice. The sites were chosen from different levels and different regions in the Sichuan province to make sure the repetitiveness of the study population. All treatment decision is made by the treating physician according to the patient’s clinical conditions; however, the multi-disciplinary team will provide consultation if required to improve the treatment of anemia. The data is collected both manually input and using software-based registry, which could increase the efficiency and reduce the typing errors. The software will be informative to assist doctors in treating dialysis patients with drug information, clinical guidelines and important alerts.

The main objective of the study is to provide the long-term impact of Roxadustat on MACE and all-cause mortality, economic burden, and safety. Differences in responding to Roxadustat in different subgroups will also be assessed. This study will be able to provide guidance in designing future, large scale randomized controlled trials assessing the impact of Roxadustat in dialysis patients.

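### As worded, the protocol has the analysis plan prepared at or after data lock, so adjustment choices in a non-randomised comparison could be made after outcomes are seen

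*Protocol article*

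**What the plan says.** The only statement on when the analysis plan is written is the last sentence of the Quality control section: "The data will be locked once the data cleaning completes, and the analysis plan will be prepared and run independently by two statisticians".

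The Data analysis section says that the comparison of primary outcomes between the ROAD cohort and the registry "will be performed using Multiple Cox regression of risk factors and propensity score method will also be applied as a sensitivity analysis".

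The Study population section describes the two groups. ROAD participants are dialysis patients with renal anemia "and on Roxadustat treatment who consent to the study". For the comparator, "The de-identified data from the provincial dialysis registry of dialysis patients with renal anemia will be serves as a control group". The Discussion adds how treatment is assigned: "All treatment decision is made by the treating physician according to the patient’s clinical conditions".

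Under Data collection, registry dialysis data are gathered "at the end of the first and second study year".

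**The concern.** In a randomised trial the allocation itself protects the primary comparison, and a late analysis plan does limited damage. Here nothing is randomised. Patients enter the ROAD cohort because a physician chose Roxadustat and the patient consented, and they are compared with registry patients selected by neither step. The estimated association therefore rests on which risk factors enter the Cox model, how the propensity score is built, and which registry patients count as controls.

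It is ordinary to leave those items to an analysis plan. The difficulty is that the one sentence that places the plan in time puts its preparation beside or behind the lock, when up to two years of outcomes are already in the database. Several defensible specifications could then be tried and one kept because of its result. A reader of the final report could not tell whether that had happened.

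**Working it through.** The point concerns the order of two steps. No figure in the protocol states it, so there is nothing to recompute. The check is a comparison of the sections.

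1. **Order within the sentence.** Three actions are listed: cleaning completes, data are locked, the plan is prepared and run. Preparing and running share one verb phrase. A final analysis can only be run after lock, so the natural reading carries preparation to the same place. The sentence contains no word such as *then* or *after* tying preparation to lock, so the order is implied only.

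2. **Any statement elsewhere that the plan comes first.** Data collection gives follow-up to week 108, yearly registry collection and yearly cost questionnaires. Data analysis names methods without dates. The Abstract, Study design, Discussion and Data Availability sections do not mention an analysis plan. Nothing moves its finalisation ahead of lock.

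3. **What is already fixed, and what is left to the plan.**

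| Item | Status in the article |
|---|---|
| Main method for primary outcomes | Fixed: multiple Cox regression (Data analysis) |
| Role of the propensity score | Fixed: sensitivity analysis (Data analysis) |
| Cost strata, hemoglobin subgroups, interaction test | Fixed (Data analysis) |
| Events that end a participant's follow-up | Fixed (Data collection) |
| Source of controls | Fixed: provincial registry dialysis patients with renal anemia (Study population) |
| Risk factors in the Cox model | Left to the plan |
| Propensity-score variables and method of use | Left to the plan |
| Detailed selection of controls within the registry | Left to the plan |

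The exposure is confined to the last three rows, which are the ones that govern confounding control.

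4. **When outcomes could be seen.** The control group's primary outcomes must come from registry data, which are collected at the end of year one and again at the end of year two. Some comparative information may therefore be available well before lock. A safeguard tied to lock alone would miss this, so it should also refer to access to outcomes by group.

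5. **Whether another safeguard covers the gap.** For event classification, the protocol says: "The main outcome of MACE will be judicated independently by two trained doctors using de-identified medical records", with a third doctor if they disagree. That protects the coding of events. It does not constrain the choice of covariates or controls.

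**The case against.** The strongest reply is that the sentence lists two quality-control measures joined by a conjunction, in loosely edited English, and need not describe a sequence. The analysis plan is not shown, and its date and version history would normally sit there. The article also fixes a good deal, as the table shows, and a missing covariate list in a journal article is not a fault.

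Most of this stands, and it narrows the point. The sequence is inferred, and the absence of covariate and propensity details is not the criticism. What remains is that the only sentence on timing points the wrong way and nothing corrects it. That is a matter of what the text says, so an unshown plan does not excuse it.

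Four stronger readings are tempting and should not be drawn:

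- **Two rival plans with two primary answers.** A reader might infer this from the phrase about independent preparation. The text refers to the plan in the singular, in a section that also describes duplicate adjudication, so one plan run twice is the more natural meaning. The wording is worth tidying, but it does not show two competing results.
- **A self-selected control group.** Physician choice and consent act on the ROAD cohort. The registry is the general comparator.
- **Censoring left open.** Data collection already lists withdrawal, change of dialysis type, transplantation and loss to follow-up as ending a participant's follow-up.
- **A bias larger than the 0.02 margin.** One could note that 250 × 0.85 ≈ 212 per cohort (equal groups assumed) gives a standard error of √(0.12×0.88/212 + 0.20×0.80/212) ≈ 0.035, which is above the margin. That is sampling error and says nothing about how far a change of covariates would move the estimate. The margin is also a risk difference, whereas the stated model is Cox regression.

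**Conclusion.** The point holds in a limited form. As printed, the protocol implies that the analysis plan is prepared at or after lock, and no section says otherwise. In a comparison that depends on adjustment, this would allow the Cox risk factors, the propensity specification and the detailed control selection to be settled after outcomes are known. The method class, the role of the propensity score and the source of controls are not at risk.

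The documents do not allow the size of any resulting bias to be estimated. The conclusion rests on the natural reading of one sentence and on there being no contrary statement in the article. If a dated plan exists that predates lock and access to outcomes by group, the remedy is simply to say so. The sentence should be corrected in either case, because the credibility of the adjusted comparison depends on it and the correction is cheap.

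**What to change.** Replace the last sentence of the Quality control section with wording to this effect: a single analysis plan, specifying the covariates for the Cox model, the selection of registry controls and the propensity-score specification, will be finalised and dated before data lock and before anyone has access to outcomes by group; after cleaning and lock, two statisticians will each run that same plan independently.

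This settles the order, covers the year-one registry collection as well as the final lock, and makes clear that the independence lies in running the plan and not in writing it.

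The cost is earlier sign-off of a document that is already planned. Both statisticians are already foreseen, so no staff or data are added.

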### Data analysis

The comparison in primary outcomes between the ROAD cohort and the registry data will be performed using Multiple Cox regression of risk factors and propensity score method will also be applied as a sensitivity analysis. The medical economic costs will be compared between ROAD cohort and registry control group using the whole population as well as populations stratified by hospital levels, regions, comorbidities.

The efficacy on HGB of Roxadustat in the treatment of anemia of the whole cohort as well as the pre-defined subgroups (including patients with evidence of erythropoietin resistance, patients with chronic inflammation, patients with impaired iron metabolism, and patients on hemodialysis or peritoneal dialysis) will be analyzed in intention-to-treat and per-protocol ROAD population. Treatment heterogeneity will be tested by adding an interaction term to the statistical models.

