**Methods/Design:**

This is a multicenter, prospective, longitudinal observational cohort study assessing if Roxadustat improves prognosis in dialysis patients. Primary outcomes will be major adverse cardiovascular events (MACE), defined as composites of cardiovascular death, myocardial infarction, cerebral infarction, hospitalization because of heart failure; all-cause mortality, and annual economic costs in two years. The data will be collected via Research electronic data capture (REDCap) based database as well as software-based dialysis registry of Sichuan province. The primary outcomes for the ROAD study participants will be compared with those in the dialysis registry cohort. Data at baseline and study follow up will also be compared to assess the association between Roxadustat and long-term clinical outcomes.

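### The non-inferiority hypothesis and 0.02 margin used to size the study for MACE are not carried into the Cox analysis or the stated aim, so the 80% power covers only one reading of the primary comparison

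*Protocol article*

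**What the plan says.** Three places in the protocol article bear on the MACE comparison.

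- **Sample size (Methods/Design, Data collection).** The target of more than 250 ROAD participants is derived "basing on noninferiority assumption with a marginal difference of 0.02 (10% of MACE incidence), actual difference of -0.08 (40% of MACE incidence"), with "α = 0.05 and 1-β = 0.8" and 15% dropout. The procedure named is "Non-Inferiority Tests for the Difference Between Two Proportions". The event rate is given as "MACE incidence of at least 20" per cent over 2 years.
- **Analysis (Methods/Design, Data analysis).** "The comparison in primary outcomes between the ROAD cohort and the registry data will be performed using Multiple Cox regression of risk factors". A propensity score method is added as a sensitivity analysis. This section mentions neither non-inferiority nor a margin.
- **Aim (Abstract, Methods/Design).** The study is described as "assessing if Roxadustat improves prognosis in dialysis patients". The abstract's Discussion, the end of the Background and the main Discussion use neutral terms instead: association, effect, impact.

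Non-inferiority and the 0.02 margin appear only in the sample-size sentence.

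**The concern.** The hypothesis that justifies the sample size is on one scale (a difference of two proportions). The model named for the primary comparison works on another (a hazard ratio). The abstract's wording of the aim points to a different hypothesis (improvement). A reader cannot tell from the article which claim about MACE the study is meant to support, or what result would support it.

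Two things are at stake. First, the 80% power may be credited to a comparison it was not calculated for. Second, with no margin on the analysis scale, a hazard ratio that does not differ significantly from 1 could be presented as showing that roxadustat is no worse. Absence of a significant difference does not show that. If the hypothesis or the scale of the margin is chosen after the data are seen, the comparison loses its confirmatory value.

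**Working it through.** **Inputs.** From the sample-size paragraph: registry 2-year MACE risk 0.20; true difference -0.08, so ROAD risk 0.12; margin +0.02; alpha 0.05; power 0.80; dropout 15%; target above 250. The article states the 20% for both cohorts; here it is taken as the registry rate. The sidedness of alpha and the number of registry controls are not stated. I assume equal groups first and then vary the ratio.

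**1. Reproducing the stated figure.** For non-inferiority on a risk difference with equal groups:

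n per group = [0.12×0.88 + 0.20×0.80] × (z_alpha + z_beta)² / (0.02 + 0.08)²

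- One-sided 0.025: 0.2656 × 7.849 / 0.01 = 208.5, so 209 per group, and 209/0.85 = 246 enrolled. Pooled variance gives 211 (249 enrolled); the Farrington-Manning variance gives 212 (250 enrolled).
- One-sided 0.05: 165-167 per group, 195-197 enrolled. This does not reproduce 250.

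So the figure is a non-inferiority calculation with equal groups at one-sided 0.025 (two-sided 0.05), and the arithmetic is sound.

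**2. Non-inferiority on the risk difference.** Evaluable per group: 250 × 0.85 = 212.5. SE = sqrt(0.2656/212.5) = 0.0354. z = 0.10/0.0354 = 2.83; power = Φ(2.83 - 1.96) = 81%.

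**3. Non-inferiority by Cox regression.** Under proportional hazards:

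- assumed HR = ln(0.88)/ln(0.80) = 0.573
- margin of 0.02 at a 20% control risk: HR = ln(0.78)/ln(0.80) = 1.113
- distance on the log scale = ln(1.113/0.573) = 0.665
- events = 212.5×0.12 + 212.5×0.20 = 25.5 + 42.5 = 68

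With SE = sqrt(1/25.5 + 1/42.5) = 0.250, power = Φ(0.665/0.250 - 1.96) = 76%. With the Schoenfeld SE, 2/sqrt(68) = 0.243, it is 78%.

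**4. Superiority, same planning values, two-sided 0.05.**

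- Risk difference: z = 0.08/0.0354 = 2.26; power 62%.
- Cox: ln(0.573) = -0.557; power 60% with SE 0.250, 63% with the Schoenfeld SE.
- For 80% power at equal groups: 329 evaluable per group (388 enrolled) on proportions, or 102 events by Schoenfeld, that is 102/0.32 = about 319 evaluable (375 enrolled).

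**5. More registry controls (superiority, 4 per ROAD patient).**

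| Method | Power |
|---|---|
| Risk difference, unpooled variance | 86% |
| Risk difference, pooled variance | 80% |
| Cox, SE = sqrt(1/25.5 + 1/170) = 0.212 | 75% |
| Cox, Schoenfeld | 88% |

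None of these figures allows for precision lost through confounder adjustment.

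**The case against.** The strongest reply is that nothing here is strictly incompatible. A Cox model can test non-inferiority against a hazard-ratio margin, and it can yield an adjusted 2-year risk difference. The Quality control section says an analysis plan will be prepared, and a confidence-interval rule commonly sits there. All of this stands. A reader might infer that the non-inferiority hypothesis will never be tested, or that the study will end in a superiority p-value. The article supports neither: it names a model, not a null value or a decision rule.

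A reader might also infer three rival hypotheses. That is too strong. Cox regression is a method of estimation, and the superiority reading rests on one phrase in the abstract while the other statements of aim are neutral.

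The change of scale alone costs little: 81% becomes 76-78%. The fall to 60-63% needs both the superiority reading and equal groups. Nor should a single figure such as 86% be quoted for four controls per patient, since the formulas range from 75% to 88%.

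Finally, it is tempting to cite the wide interval expected if the two risks are truly equal (half-width 1.96 × sqrt(2×0.16/212.5) = 7.6 points at equal groups, against a 2-point margin). That imprecision comes from sizing on an assumed 8-point benefit and would remain after the fix, so it is not evidence for this point.

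What survives is that the article itself states the sizing hypothesis, the primary model and the aim, and they do not match. A later analysis plan could repair this only by making the choice that the article leaves open.

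**Conclusion.** The concern holds as an inconsistency between sample size, analysis and aim. The sample-size arithmetic is correct, and Cox regression is not in itself a wrong choice. The non-inferiority hypothesis and its 0.02 margin stop at the sample-size sentence, and the 80% power belongs to that test alone.

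At 212.5 evaluable per group and equal groups, power is about 81% for non-inferiority on the risk difference, 76-78% for non-inferiority by Cox against HR 1.11, and 60-63% for superiority. At four controls per patient, superiority power is 75-88%. These figures rest on risks of 12% and 20%, two-sided 0.05, proportional hazards for the Cox figures, and a control ratio that the article does not state. A larger registry group can recover much of the power for superiority, but it does not settle which hypothesis is primary or how the hazard ratio is to be judged.

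**What to change.** State one primary hypothesis for MACE and use it in the abstract's aim, the sample-size paragraph and the Data analysis section.

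- **If non-inferiority is kept:** pre-specify the margin on the scale of the analysis. Either declare non-inferiority when the upper limit of the two-sided 95% CI for an adjusted 2-year risk difference, standardised from the Cox model, is below 0.02; or use an upper limit below HR 1.11, noting that this assumes a 20% control risk and proportional hazards. Superiority may then be tested in fixed sequence, only after non-inferiority is shown, with no cost in alpha. Say explicitly that a non-significant difference will not be read as non-inferiority.
- **If superiority is the aim:** restate the power for that test and give the registry-to-ROAD ratio it relies on.

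The first option costs wording and, for the risk difference, one standardisation step, with no new data. The second needs a recalculation and, if few registry controls are available, possibly a larger ROAD cohort. Either choice should be made before outcome data are examined.
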